### Data collection and diagnoses

2.10

Patient demographic data mainly include: (1) GA, birth weight, singleton or multiple births, sex, prenatal steroid use, mode of delivery, presence of intrauterine distress, and maternal pregnancy complications; and (2) Apgar scores at 1 min, 5 min, and 10 min, as well as umbilical cord blood gas analysis.

Clinical information at each time point (at admission, 1 h after birth, 4–10 h after PS administration, 24 h, 72 h, 7 days, 14 days, 28 days, and before discharge or at 36 weeks CA) include (1) timing, dosage, and method of the initial PS administration; (2) SAS, respiratory machine mode, oxygen saturation index, and FiO_2_ levels at each time point; and (3) LUS at each time point. LUS will collect individual scores for each lung field as well as the total score.

Complications and outcomes: (1) Respiratory complications: this includes the occurrences of infectious pneumonia, pneumothorax, pulmonary hemorrhage, and BPD, along with their severity grading; (2) Cardiovascular complications: specifically, hemodynamically significant patent ductus arteriosus (hsPDA); (3) Other complications in premature infants: these encompass IVH, periventricular leukomalacia, NEC, late-onset sepsis, ROP, intrauterine growth restriction, and more; and (4) Length of hospital stay and associated costs.

BPD diagnosis will adhere to the 2018 National Institute of Child Health and Human Development (NICHD) classification. Diagnosis of hsPDA will rely on clinical signs and echocardiography (20). IVH and white matter injury will be diagnosed via cranial ultrasound, with IVH graded using the Papile classification (21). NEC staging will follow modified Bell criteria (22). ROP diagnosis and staging will be based on fundoscopic examinations conducted by ophthalmologists.

### Safety procedures

2.11

Throughout the study duration, researchers will continuously monitor all enrolled infants to ensure their safety. Any occurrence of severe or significant adverse events will be promptly reported to the principal investigator for assessment. This study strictly adheres to the principles of human subject protection, and in the event of adverse events, regardless of their association with the study, the trial will be promptly terminated.

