### Outcome measures

2.9

The primary outcome measure for this study is the duration of mechanical ventilation (both invasive and non-invasive) during hospitalization in the ultrasound and control groups. Secondary outcome measures encompass: (1) the utilization rate of PS in both groups; (2) the proportion of infants receiving the first dose of PS early (within 3 h after birth) and the time from birth to the initial PS administration; (3) the oxygen concentration and the worst oxygenation index (OI) at different time points following PS administration; (4) LUS at various intervals following PS administration (at 3 days, 7 days, 14 days, 28 days, and before discharge/at 36 weeks CA; and (5) the incidence rates of major complications in preterm infants such as BPD, intraventricular hemorrhage (IVH), retinopathy of prematurity (ROP), and necrotizing enterocolitis (NEC).

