### Sample size calculation

2.12

With the duration of mechanical ventilation as the primary outcome measure for both groups, we anticipate that patients in the conventional treatment group will require an average of 96 ± 12 h of respiratory support based on previous departmental data. It is expected that integrating ultrasound diagnosis will promptly improve respiratory function, reducing the mechanical ventilation duration to an average of 86 ± 12 h. To compare the difference in mechanical ventilation duration between the groups, a two-sample independent *t*-test will be employed, setting α at 0.05 and ensuring a power of 80%. With a 1:1 ratio between the groups, sample size estimation using PASS15 indicates that each group will require 24 patients, totaling 48 patients. Considering the potential risk of underestimating sample size due to low effect size and dropout rates, the actual sample size will be 60 patients (48 ÷ 80% = 60), with 30 patients in each group.

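### Section 2.11 ends the whole trial on adverse events whatever their cause, which conflicts with the complication outcomes, the infant-level handling of serious events and the target of 60

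*Protocol article*

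**What the plan says.** Section 2.11 (Safety procedures) has two relevant sentences. The first deals with reporting: "Any occurrence of severe or significant adverse events will be promptly reported to the principal investigator for assessment". The second gives the consequence: "in the event of adverse events, regardless of their association with the study, the trial will be promptly terminated". What is terminated is the trial, not an infant's participation, and a causal link to the study is expressly not required. Nothing elsewhere in the article qualifies this.

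Other sections assume a trial that carries on after such events:

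- Section 2.9 makes complications a secondary outcome: "the incidence rates of major complications in preterm infants such as BPD, intraventricular hemorrhage (IVH"), with ROP and NEC also named. Section 2.10 adds pneumonia, pneumothorax, pulmonary hemorrhage, hsPDA, late-onset sepsis and others. Table 1 records complication percentages at 36 weeks CA or discharge.
- Section 2.2.2 excludes infants who die within 72 h of birth, while sections 2.3 and 2.7 randomize on arrival in the NICU.
- Section 2.8 lists pulmonary hemorrhage and respiratory or cardiac arrest among the indications for intubation and ventilation.
- Section 2.12 fixes the size: "the actual sample size will be 60 patients (48 ÷ 80% = 60), with 30 patients in each group".

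**The concern.** A rule that stops a trial normally names the kind of event, a threshold, and who reviews it. This one names only adverse events and waives relatedness. The population is infants below 32 weeks with respiratory distress, followed to discharge or 36 weeks CA, and the protocol itself expects enough complications to report their incidence by arm. If those complications count as adverse events, the first one ends the trial. The secondary comparison then cannot be made, and the primary comparison rests on whatever number had been enrolled. If the sentence is not followed, the trial departs from the only stopping rule the article states, and nothing usable replaces it. In an unblinded trial in newborns, neither position is satisfactory.

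**Working it through.** **1. The planned size.** Inputs from section 2.12: control "will require an average of 96 ± 12 h of respiratory support"; ultrasound group "reducing the mechanical ventilation duration to an average of 86 ± 12 h"; alpha 0.05 (two-sided assumed, as sidedness is not stated); power 80%; 1:1 allocation.

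- Normal approximation: n = 2 × (1.960 + 0.842)² × 12² / 10² = 22.6, so 23 per group.
- Noncentral t: power is 78.9% at 23 per group and 80.7% at 24.
- This reproduces "each group will require 24 patients, totaling 48 patients", and 48 / 0.80 = 60.

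The sample size arithmetic is therefore not at fault. The question is whether the trial can get there under section 2.11.

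**2. The literal rule.** Let p be the probability that an infant has at least one adverse event. The documents do not give p, so it is an assumption shown over a range. With independent infants and prompt detection:

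- P(60 infants without an event) = (1 − p)^60
- Mean number of infants up to and including the first event = 1/p
- Median = smallest k with (1 − p)^k ≤ 0.5

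| Assumed p | P(60 event-free) | Mean infant of first event | Median infant of first event |
|---|---|---|---|
| 0.01 | 55% | 100th | 69th |
| 0.02 | 30% | 50th | 35th |
| 0.05 | 4.6% | 20th | 14th |
| 0.10 | 0.18% | 10th | 7th |
| 0.20 | 0.0000015 (as a proportion) | 5th | 4th |

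**3. What a stop does to the primary comparison.** Under the section 2.12 assumptions, stopping at the mean for p = 0.05 (20 infants, 10 per group) leaves power of 42%. Stopping at the mean for p = 0.10 (10 infants, 5 per group) leaves 21%.

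**4. Late detection.** BPD and ROP are recorded at 36 weeks CA or discharge (Table 1), so the stop would lag behind enrolment. Section 2.1 gives about 200 very preterm births a year, or 200/52 = 3.8 a week. An infant born at 30 weeks reaches 36 weeks CA 6 weeks later, after at most about 6 × 3.85 = 23 further births (not all would be eligible). If every event were known only then, 60 − 23 = 37 infants would have to be event-free for enrolment to reach 60. The chance is 0.98^37 = 47%, 0.95^37 = 15%, 0.90^37 = 2.0% or 0.80^37 = 0.026%. The lag is longer for less mature infants. Early events, such as pneumothorax or pulmonary hemorrhage, would carry little lag.

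**5. The passages side by side.** Section 2.2.2 treats a death within 72 h as the exclusion of one infant, and section 2.8 treats pulmonary hemorrhage and cardiac arrest as reasons to ventilate that infant. Invasive ventilation is part of the primary outcome in section 2.9. Each of these presupposes that the trial continues after an event which, under the wording of section 2.11, would end it.

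**The case against.** The best defence is that the authors did not mean what the sentence says. Three readings are open:

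- The sentence may refer back to the severe or significant events named just before it.
- The listed complications are called complications and not adverse events, a term the article does not define, so they may be meant as a separate class.
- The word trial may be loose wording for one infant's participation, which would fit sections 2.2.2 and 2.8.

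Each is a possible intention, but the text states none of them. The severe-only reading does not rescue the rule either: the first severe event, even one unrelated to the study, would still end the trial.

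Parts of the defence do stand. A reader might infer that the trial would stop after the first few infants. That needs an event rate of about 20% or more and immediate detection. The documents give no rate, and some listed events are diagnosed weeks later. A reader might also infer that section 2.11 contradicts itself by sending severe events for assessment and then terminating. That clash is weak, because assessment can precede termination. The firm conflict is with the other sections.

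**Conclusion.** The concern holds as a stated rule that is wrong as written. Section 2.11 cannot be followed literally alongside sections 2.2.2, 2.8, 2.9, 2.10 and 2.12. If any adverse event counts, reaching 60 is unlikely: below 5% once 5% or more of infants have an event, on the assumptions of independence and prompt detection. Late-diagnosed events raise that figure (to about 15% at 5% per infant in the delayed case above) but do not change the conclusion at 10% or more. At 2% or less, 60 remains reachable with real probability, so the size depends on a rate the documents do not supply. The conflict between the sections does not depend on that rate.

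It would go too far to say that no primary result is possible or that the trial is in continuous violation of its protocol. Both follow only from the most literal reading combined with an assumed event rate.

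**What to change.** Amend section 2.11 and reconcile it with sections 2.2.2, 2.8, 2.9, 2.10 and 2.12:

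1. Remove automatic termination of the whole trial on any adverse event.
2. State that the complications listed in sections 2.9 and 2.10 are recorded and analysed as outcomes and do not by themselves end the trial.
3. Separate the end of one infant's participation from termination of the trial.
4. Have the sponsor and the Ethics Committee state which events, after whose review, can end the trial, without barring the investigator or sponsor from stopping for safety.

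The last point is theirs to settle. Section 2.4 says only that the trial runs under Ethics Committee supervision. It does not describe a review of events by arm, so that task should not be assumed to be in place already.

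The cost is one paragraph by amendment. Sample size, treatment and outcomes do not change. Any further cost depends on who is named to review events.

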### Sample size calculation

2.12

With the duration of mechanical ventilation as the primary outcome measure for both groups, we anticipate that patients in the conventional treatment group will require an average of 96 ± 12 h of respiratory support based on previous departmental data. It is expected that integrating ultrasound diagnosis will promptly improve respiratory function, reducing the mechanical ventilation duration to an average of 86 ± 12 h. To compare the difference in mechanical ventilation duration between the groups, a two-sample independent *t*-test will be employed, setting α at 0.05 and ensuring a power of 80%. With a 1:1 ratio between the groups, sample size estimation using PASS15 indicates that each group will require 24 patients, totaling 48 patients. Considering the potential risk of underestimating sample size due to low effect size and dropout rates, the actual sample size will be 60 patients (48 ÷ 80% = 60), with 30 patients in each group.

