Criteria for discontinuation of non-invasive ventilation: (1) more than 72 h after birth; (2) a PEEP of 3–5 cmH2O or less during NCPAP, or an MAP of less than 6–7 cmH2O during NIPPV; (3) an FiO_2_ of 25% or less; (4) an SAS of less than 3; and (5) absence of respiratory pauses or bradycardia requiring stimulation for recovery. If all five conditions are met and sustained for over 24 h, discontinuation of non-invasive ventilation may be considered based on clinical assessment. If any of the following conditions arise after discontinuation of non-invasive ventilation, encompassing: (1) an FiO_2_ of more than 0.25 and an SpO2 of less than 85%; (2) an SAS of more than 3; or (3) three or more episodes of spontaneously recoverable respiratory pauses or bradycardia within 24 h, non-invasive ventilation will be reinstated. Reassessment for discontinuation of non-invasive ventilation will not be conducted until at least 48 h later.

All study participants will receive caffeine citrate within 24 h after birth to prevent respiratory pauses, with an initial loading dose of 20 mg/kg and a maintenance dose of 5–10 mg/kg per day.

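### On a literal reading of the rule for ending non-invasive ventilation, the planned means of 86 h and 96 h (SD 12 h) are not attainable, so the stated 80% power is unsupported

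*Protocol article*

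**What the plan says.** All references are to the protocol article.

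- **Outcome (2.9 Outcome measures).** The primary outcome is "the duration of mechanical ventilation (both invasive and non-invasive) during hospitalization in the ultrasound and control groups".
- **Planning values (2.12 Sample size calculation).** Control infants "will require an average of 96 ± 12 h of respiratory support based on previous departmental data". The ultrasound arm is expected to do better, "reducing the mechanical ventilation duration to an average of 86 ± 12 h". A two-sample t-test at α = 0.05 with 80% power and 1:1 allocation gives 24 per group, raised to 30 per group (60 in total).
- **Ending non-invasive ventilation (2.8 Therapy).** The first of five conditions is "1) more than 72 h after birth". The section then states: "If all five conditions are met and sustained for over 24 h, discontinuation of non-invasive ventilation may be considered based on clinical assessment".
- **After a restart (2.8 Therapy).** "Reassessment for discontinuation of non-invasive ventilation will not be conducted until at least 48 h later".
- **Start of support (2.7 Planned intervention).** Non-invasive or invasive support by T-piece is given during resuscitation and transport, so it begins close to birth.
- **Analysis (2.13 Statistical analysis).** t-test for normally distributed continuous data, Mann-Whitney for the rest.

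**The concern.** The rule for ending support and the planning values describe the same quantity. The age condition is one of the five, and all five have to hold for more than 24 h. An infant first satisfies the age condition at 72 h, so on the plain wording the earliest stop is at about 72 + 24 = 96 h of age. For an infant supported from birth, that is also the shortest possible duration. The planned ultrasound mean of 86 h lies below this minimum. A symmetric control distribution centred on 96 h needs half its infants below it.

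Such a floor would apply to both arms and would absorb part of any difference between them. This is the only outcome for which the trial is powered. If the planning scenario cannot occur, a null result could be read as evidence against ultrasound guidance without anyone knowing what the trial was able to detect.

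The SD of 12 h raises a second question. The outcome runs over the whole hospital stay, and an infant put back on support stays on it for at least 48 h more, which is 48 ÷ 12 = 4 planned SDs.

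**Working it through.** **1. The plan's own figure.** Inputs from 2.12: difference 96 − 86 = 10 h, SD 12 h, α = 0.05 (sidedness not stated; two-sided reproduces the figure), power 80%, 1:1.

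- Normal approximation: n = 2(1.960 + 0.842)² × 12² ÷ 10² = 22.6, so 23 per arm.
- Exact noncentral t with d = 10/12 = 0.833: n = 23.6, so 24 per arm, as stated.
- Power by the same method: 80.7% at 24 per arm and 88.8% at 30 per arm.
- Inflation: 48 ÷ 0.80 = 60, as stated.

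**2. Share of the planned distributions below the floor.** P(X < f) = Φ((f − mean)/12).

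| Floor f | Control, mean 96 | Ultrasound, mean 86 |
|---|---|---|
| 96 h (literal reading) | Φ(0) = 50% | Φ(0.833) = 80% |
| 72 h (24 h may run before 72 h of age) | Φ(−2) = 2% | Φ(−1.167) = 12% |

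**3. Illustration: values below the floor are held at it.** With z = (f − m)/12, the mean becomes f·Φ(z) + m·(1 − Φ(z)) + 12·φ(z).

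- Floor 96 h, control: 96 × 0.5 + 96 × 0.5 + 12 × 0.399 = 100.8 h (SD 7.0).
- Floor 96 h, ultrasound: 96 × 0.798 + 86 × 0.202 + 12 × 0.282 = 97.4 h (SD 3.7).
- Difference: 3.4 h instead of 10 h.
- Floor 72 h: means 96.1 and 86.7 h, difference 9.4 h.

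Simulated power (40,000 trials per t-test cell; Mann-Whitney from at least 8,000), at 24 / 30 per arm:

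| Floor | t-test | Mann-Whitney |
|---|---|---|
| 96 h | about 57% / 68% | about 63% / 74% |
| 72 h | about 80% / 88% | about 79% / 87% |

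These figures depend on the model. If the normals are truncated at the floor instead of held at it, the difference is 2.9 h and t-test power is 31% / 38% at 96 h. At 72 h the difference is 7.9 h and power is 71% / 80%.

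**4. What moves power and what does not.** Power depends on the difference divided by the SD. If both means were higher but still 10 h apart with SD 12 h, power would stay at 81% / 89%. If the 10 h difference is kept and the SD is larger (an assumption, since the documents give no other SD), t-test power at 24 / 30 per arm is 47% / 56% for SD 18 h and 29% / 35% for SD 24 h.

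**The case against.** The strongest reply has four parts.

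- **The calculation is right.** This stands. Both 24 per arm and the inflation to 60 reproduce, and 30 per arm has 88.8% power on the stated inputs. The issue lies in the inputs.
- **The 96 h floor depends on one reading.** Age is not a state that one naturally calls sustained. The rule can be read as 24 h of stability in the other four conditions plus age over 72 h. Both planned means are then attainable and the floor matters little. This is a fair reading, but the text says all five, so it has to be settled in the text. The rule also governs only non-invasive support: an infant extubated straight to no support, one who dies after 72 h, or one whose support starts well after birth could have a total below 96 h.
- **Lower power does not follow.** A reader might infer that the trial is shown to have less than 80% power. The documents do not support that. The absolute means do not determine power, the figures under a 96 h floor come from an illustrative model, and 2.13 provides a rank test that loses less in that illustration.
- **The SD may be right.** It accompanies a mean said to come from departmental data. If those data already include reinstated infants and long courses, adding them again would count them twice. The documents give no rate for either, so no specific lower power can be derived from the restart rule. What remains is that the article does not say whether the departmental figure describes this endpoint under this rule.

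**Conclusion.** The point holds as a conflict between stated passages. On the literal wording of 2.8, non-invasive support begun at birth cannot end before about 96 h. Section 2.12 nevertheless plans means of 86 h and 96 h with SD 12 h for an outcome that includes that support. On that reading the 80% power rests on inputs that the protocol's own rule does not permit, and it is unsupported.

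The size depends on the reading. With a 96 h floor and planned values held at it, the detectable contrast falls from 10 h to 3.4 h, and power at 24 / 30 per arm is about 57% / 68% by t-test or 63% / 74% by Mann-Whitney. With a 72 h floor on the same basis it stays near 80% / 88%. Both rest on normal planning distributions, support from birth and the same rule in both arms. No single corrected power can be given.

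The SD of 12 h is a separate item to check. It is not shown to be wrong.

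**What to change.** 1. Reconcile 2.8, 2.9 and 2.12. State how age over 72 h and the 24 h period combine, and from what time the hours of support are counted. Which rule applies is for the clinicians to decide.
2. Confirm that the departmental 96 ± 12 h is total invasive plus non-invasive time over the hospital stay, restarts included, under the rule that will apply. If it is not, take the mean and SD of exactly that endpoint from the same data.
3. Restate the power, or the detectable difference, for the fixed 60 infants with those values and the test that the distribution calls for under 2.13. Drop the 80% claim if it does not hold.

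The cost is a re-run on data that the department already cites and a few revised sentences. No extra infants are needed. The downside is that the stated power may become less favourable.

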### Statistical analysis

2.13

The demographic and clinical characteristics of both the ultrasound and control groups will be described using means and standard deviations, medians and ranges, or ratios and percentages. Statistical analyses will be conducted using SPSS 20.0 software. Normally distributed continuous data will be presented as means ± standard deviations, with inter-group comparisons assessed using independent two-sample *t*-tests. Non-normally distributed continuous data will be presented as M (Q1, Q3), with inter-group comparisons analyzed using the Mann-Whitney *U*-test. Categorical data will be expressed as counts (%), and inter-group comparisons will be evaluated using the *χ*^2^ test, continuity-corrected *χ*^2^ test, or Fisher's exact test. A *P*-value of less than 0.05 will be considered statistically significant.

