**Figure 1 F1:**
[figure not shown]
Fowchart of participant selection and treatment.

All very preterm infants will undergo antenatal consultations before birth. Neonatologists will engage in thorough discussions with the parents of premature infants, informing them about the risks associated with premature birth at this GA and outlining the treatment process post-birth. Before delivery, a neonatal resuscitation team comprising neonatal and obstetric specialists will be established. Following delivery, premature infants will be transferred within the hospital using transport incubators, and a T-piece resuscitator will be utilized during the transfer process. Within 1 h after birth, all enrolled infants will undergo lung ultrasonography, and those meeting the diagnostic criteria will receive PS as per the trial protocol. Subsequently, they will undergo regular lung ultrasound monitoring until discharge or at 36 weeks corrected age (CA).

Centers participating in the study routinely use lung ultrasonography. Two ultrasound physicians and five neonatologists will participate in this study. Both ultrasound physicians have received comprehensive training in lung ultrasonography and LUS application. Lung ultrasonography will be performed by two ultrasound physicians, who each have more than 2 years of experience in neonatal lung ultrasound and have received systematic training before the study, including study protocols, lung ultrasound scoring, and interpretation of lung ultrasound images. In order to ensure the consistency of scoring results, the two doctors will respectively determine the LUS based on ultrasound images. If the scores are consistent, the results will be recorded. If the score difference is ≥2, the final score will be determined by the two doctors after discussion.

Other research personnel have completed standardized training, including familiarization with the trial protocol, methods of recording case records, and criteria for assessing complications.

Lung ultrasonography will be conducted using the Mindray M9 ultrasound system equipped with a linear, high frequency (10–15 MHz) transducer.

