### Assessment points

2.6

The main assessment and recording of the infants’ indicators will occur at the following time points (Table 1).

**Table 1 T1:** Neonatal assessment chart.

Measure	Assessment point							
	Allocation within 1 h after birth	4–10 h after PS	24 h	3 days	7 days	14 days	28 days	36 weeks CA/discharge
LUS	×	×	×	×	×	×	×	×
Clinical index								
Silverman Anderson score	×	×	×	×	×	×	×	×
Respiratory support mode	×	×	×	×	×	×	×	×
Ventilator parameters	×	×	×	×	×	×	×	×
Medication use of PS	×		×					
Outcomes assessment								
NIV (hours)								×
IMV (hours)								×
Supplemental oxygen (days)								×
PS (%)								×
Early PS (%)								×
Birth to the application of 1st PS (min)								×
LOS								×
Costs associated with hospital care								×
Complications								
hsPDA (%)								×
BPD (%)								×
IVH (%)								×
NEC stage I or II (%)								×
ROP (%)								×

NIV, non-invasive ventilation; IMV, invasive mechanical ventilation; Early PS, pulmonary surfactant administered within 3 h after birth; LOS, length of stay; hsPDA, hemodynamically significant patent ductus arteriosus; IVH, intraventricular hemorrhages; BPD, bronchopulmonary dysplasia; NEC, necrotizing enterocolitis; ROP, retinopathy of prematurity.

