**Figure 2 F2:**
[figure not shown]
Calculating lung ultrasonography scores. Segmentation: Each lung is divided into 3 regions (anterior L12/R12, lateral L34/R34, and posterior L56/R56), totaling 6 regions. Scoring: The higher the score, the more severe the condition, with a total score of 18 points. The detailed scoring criteria are as follows: (**A**) 0 points indicate normal lung ventilation, characterized by A-lines with sporadic B-lines; (**B**) 1 point signifies moderate reduction in lung ventilation, including fused B-lines and interstitial syndrome (B-line accumulation <50% of the lung field examined); (**C**) 2 points denote severe reduction in lung ventilation, with a small amount of localized subpleural consolidation (B-line accumulation ≥50% of the lung field examined; B-line covers more than half of the intercostal space); (**D**) 3 points represent extensive lung consolidation.

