#### Control group

2.7.2

In cases where clinical diagnosis confirms NRDS, PS will be administered at a dosage of 200 mg/kg (Poractant Alfa, Curosurf®). LISA will be employed for infants in a non-invasive ventilation state, while those in an invasive ventilation state will receive PS via endotracheal tube. If clinical manifestations do not meet the diagnosis of NRDS, PS will not be administered.

All enrolled infants will undergo lung ultrasound scoring at 24 h, 3 days, 7 days, 14 days, 28 days, and 36 weeks CA (prior to discharge) (with scoring results withheld from the clinical team).

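### Follow-up lung ultrasound score is compared without adjustment for the first score, giving up precision at little cost; the planned tests are valid

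*Protocol article*

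**What the plan says.** Section 2.9 lists as secondary outcome 4 "LUS at various intervals following PS administration (at 3 days, 7 days, 14 days, 28 days, and before discharge/at 36 weeks CA". Figure 2 defines the score over six regions, each scored 0 to 3, "with a total score of 18 points".

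Section 2.13 gives the only analysis rule for continuous data. Normal data are handled "with inter-group comparisons assessed using independent two-sample" t-tests. For the rest: "Non-normally distributed continuous data will be presented as M (Q1, Q3), with inter-group comparisons analyzed using the Mann-Whitney" U-test. It names no covariate, change score or repeated-measures model.

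Three places plan a first LUS without limiting it to one arm:
- Section 2.1: "Within 1 h after birth, all enrolled infants will undergo lung ultrasonography".
- Table 1 (section 2.6) marks LUS in the column "Allocation within 1 h after birth".
- Section 2.10 records LUS at each time point, including admission and 1 h after birth: "LUS will collect individual scores for each lung field as well as the total score".

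Three places are narrower. Section 2.7.1 describes the first scan for the ultrasound group only. Section 2.7.2 says "All enrolled infants will undergo lung ultrasound scoring at 24 h, 3 days, 7 days, 14 days, 28 days, and 36 weeks CA", a list that begins at 24 h. The Discussion, in its point on scan timing, attributes the first-hour scan to the ultrasound group.

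Section 2.3 describes 1:1 randomisation with no stratification stated.

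**The concern.** The starting value of an outcome is often its best single predictor. Here it is the same 0 to 18 score, and the protocol itself treats early LUS as a measure of disease severity. With about 30 infants per arm and no stratification stated, the arms may differ in starting LUS by chance. An unadjusted comparison at day 3 or day 7 leaves that variation in the estimate, although the data to remove it are due to be collected. At stake is the width of the confidence interval for a secondary outcome and how readily an observed difference can be separated from a difference in starting severity. The primary outcome, ventilation duration, is not affected.

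**Working it through.** **Inputs from the article.** Planned size 30 per arm; alpha 0.05 (taken as two-sided, since sidedness is not stated); power 80%; primary outcome 96 v 86 h with SD 12 h (section 2.12). LUS ranges from 0 to 18 (Figure 2).

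**Assumed.** rho, the within-arm correlation between first and later LUS. The documents give none, so a range is shown.

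**1. The plan's own figure.** Standardised effect = 10/12 = 0.833. The t-test needs 23.6, so 24 per arm (power 0.807), and 48/0.80 = 60. The stated sample size reproduces. It concerns ventilation hours; no size, effect or power is stated for LUS.

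**2. Unadjusted reference for LUS.** With n = 30 per arm, the t-test has 80% power for a difference of 0.736 SD.

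**3. Adjusted variance.** With one estimated covariate, the variance relative to the unadjusted comparison is

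(1 − rho²) × [1 + 1/(2n − 4)] = (1 − rho²) × (1 + 1/56) = (1 − rho²) × 1.018.

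The detectable difference is 0.736 × √(factor), and the equivalent size is 30/factor. Power is for the same 0.736 SD effect, from the noncentral t with 57 degrees of freedom.

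| rho | variance factor | detectable difference (SD) | equivalent n per arm | power |
|---|---|---|---|---|
| 0 | 1.018 | 0.742 | 29.5 | 79.3% |
| 0.3 | 0.926 | 0.708 | 32.4 | 82.9% |
| 0.4 | 0.855 | 0.680 | 35.1 | 85.7% |
| 0.5 | 0.763 | 0.643 | 39.3 | 89.4% |
| 0.6 | 0.651 | 0.594 | 46.1 | 93.4% |

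Break-even is where (1 − rho²) × 57/56 = 1, so rho² = 1/57 and rho = 0.13.

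**4. Chance imbalance.** The SD of the between-arm difference in first LUS is √(2/30) = 0.258 SD, so its 95% range is ±1.96 × 0.258 = ±0.51 SD. The probability of exceeding 0.25 SD is 33%, and of exceeding 0.5 SD about 5%. The unadjusted follow-up difference carries rho × imbalance. At rho 0.5, a 0.25 SD imbalance shifts it by 0.125 SD, and the extreme 0.51 SD by about 0.25 SD.

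**5. Bounded score and rank tests.** A simulation (3,000 runs per setting, 30 per arm) used scores rounded and clipped to 0 to 18, with assumed mean 8 and SD 3.5 for the first LUS and mean 6 and SD 3 for the later one. At a true difference of 0.74 SD:

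| rho | t-test | ANCOVA | Mann-Whitney | rank ANCOVA |
|---|---|---|---|---|
| 0 | 0.80 | 0.80 | 0.78 | 0.78 |
| 0.3 | 0.80 | 0.83 | 0.78 | 0.81 |
| 0.5 | 0.80 | 0.89 | 0.78 | 0.87 |

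With no true difference, the two planned tests rejected in 4.6% to 5.2% of runs over rho from 0 to 0.7.

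**The case against.** **The planned tests are valid.** This stands. Type I error stays near 5%, the estimate is unbiased over repeated randomisation, and the confidence interval already allows for chance imbalance. A reader might infer that unadjusted tests make a false finding on LUS more likely than 5%; nothing in the documents or the calculation supports that.

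**The gain rests on an unknown correlation.** This also stands. At rho 0.3 the gain is about 3 points of power. Outcome visits start at day 3, when many infants will have had surfactant, and run to 36 weeks, so the correlation probably weakens and late visits may gain little.

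**The first score is not a clean baseline.** Infants are randomised on ward admission (section 2.7). In the ultrasound group the scan follows within 1 h of admission (2.7.1), and the ultrasound physicians know the arm (2.5). A score above 8 with ultrasound-confirmed RDS triggers surfactant in that arm only, so scoring could differ by arm. A scoring shift would bias the adjusted difference by about rho × shift: an assumed 0.25 SD shift at rho 0.5 gives 0.125 SD. The unadjusted comparison does not have this weakness. The objection calls for safeguards but does not remove the case for adjusting, provided both results are reported.

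**Controls may not have the first scan.** A reader of 2.7.1, 2.7.2 and the Discussion alone might infer this. Sections 2.1, 2.6 and 2.10 plan it for all infants, and nothing says that controls are left out. The passages need reconciling, but they do not show that the covariate is missing.

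**A statistical analysis plan could add covariates.** It could, but section 2.13 names the tests for all continuous data and does not defer the choice.

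**Conclusion.** The point holds as one of efficiency on a secondary outcome, and it is minor. Section 2.13 fixes an analysis of follow-up LUS that cannot use a starting value which the protocol plans to collect in all infants. Under assumed correlations of 0.3 to 0.6, adjustment cuts the variance by about 7% to 35% and raises 80% power to about 83% to 93%. Below a correlation of about 0.13 it gains nothing, and at zero it costs about 2% in variance. These figures assume that all 30 infants per arm contribute. At 24 per arm the unadjusted detectable difference is 0.83 SD, and the variance factor at rho 0.5 is almost the same (0.75 × (1 + 1/44) = 0.767). The benefit is most plausible at the early visits. It also rests on first scores that are taken before any surfactant and read alike in both arms, which the present design does not guarantee.

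**What to change.** **In section 2.13**, state that LUS at each outcome visit is compared in all randomised infants, whether or not they received surfactant. Use ANCOVA with arm and the first LUS taken before any surfactant (rank-based if scores are clearly skewed), or one mixed model over visits with arm, time, arm-by-time and that first LUS. Report the adjusted difference with its 95% CI, and keep the t-test or Mann-Whitney result as a sensitivity analysis.

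**Safeguard for the covariate.** Before relying on the adjusted result, compare the distribution of the first LUS between arms, including around the threshold of 8. If the distributions are not similar, interpret the adjusted and unadjusted results together. This check has limits: a difference above 0.25 SD arises by chance in a third of trials of this size, so it will show only gross differences in scoring.

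**Consistency.** Reconcile sections 2.7.1, 2.7.2 and the Discussion with sections 2.1, 2.6 and 2.10, so that the first scan is clearly stated for the control arm.

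**Cost.** A few sentences, a standard procedure in the named software and one degree of freedom. No extra infants are needed, and no extra scans beyond those that 2.1, 2.6 and 2.10 already plan. The downside is reliance on a first score read with the arm known. The choice should be fixed before outcome data are seen.
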